#### 1.b. Overview

A multicenter-center Phase IIa, double-blind, randomized controlled trial of a 600 mg dose of mifepristone and placebo is being proposed to determine whether there is sufficient evidence of a signal for short-term (one and three months) efficacy in veterans with chronic PTSD to warrant a Phase III trial. For this, 90 veterans with PTSD will be randomized to either mifepristone or placebo. To determine whether there is a signal, we will use statistical selection theory (see Simon et al., 1985). The final outcome will compare the proportion of clinical responders one month after treatment under the scenario: mifepristone 600 mg/day for 7 days vs. placebo. A clear benefit of this method is that it requires a much smaller sample size than traditional hypothesis testing, resulting in a reduction of both clinical costs and adverse events; this approach is widely used for Phase II drug development and testing in the pharmaceutical industry to determine whether to pursue further clinical testing of a specific compound. Based on the outcome of this exploratory trial, we will make a determination regarding whether to pursue a larger and more definitive Phase III study of mifepristone.

The innovation of studying mifepristone is twofold. The first is the application of this glucocorticoid receptor antagonist to the treatment of PTSD, which has not been studied before. The second is the use of a short-term dosing strategy that is novel in the context of classic pharmacological treatment of mental disorders. Whereas most pharmacological treatments are recommended for long-term use, the available data suggest that short-term use of a high dose of mifepristone can have enduring effects through a re-setting of the HPA axis. Short-term or intermittent dosing strategies may be particularly appealing to veterans, as complaints regarding side effects associated with long-term pharmacotherapy are common. If the initial trials in PTSD are successful, subsequent studies could assess myriad potential clinical applications in PTSD including single or intermittent dosing as monotherapy, as an adjunctive treatment to enhance or accelerate the effects of other pharmacological treatments or psychotherapy, and for PTSD prophylaxis following traumatic stress.

The CCTA mechanism is being pursued since the ultimate goal is to develop a pharmacological treatment strategy that is efficacious in veterans with PTSD. The use of this mechanism will ensure that adequate clinical, scientific, and pharmaceutical oversight and resources will be available to pursue this goal; Phase II trials fall within the purview of the CCTA mechanism.

In this initial trial we propose to study the effects of mifepristone in veterans with PTSD in order to better detect a signal if there is one. Consistent with previous studies in neuropsychiatric disorders (Belanoff et al., 2002; Young et al., 2004; Gallagher et al., 2005; DeBattista et al., 2006; Gallagher et al., 2008; Blasey et al., 2009), participants will be treated daily for one week with a high dose of mifepristone (600 mg/day) or placebo and clinical outcomes will be determined at one month. The primary outcome will be the clinical responder rate, with responders defined as a 30% reduction in the total PTSD symptom severity score (past week symptom status) from baseline to four weeks derived from the Clinician Administered PTSD Scale (CAPS). This definition of responder status has been used consistently in PTSD clinical trials. The response will be based on the change in CAPS (past week symptom status) score from baseline to four weeks. To evaluate the durability of the effects of this short-term treatment, participants will be assessed for up to three months.

#### 1.c. Specific Objectives

##### 1.c.1. *Primary Objective*

1.c.1.a. To determine whether 600 mg of mifepristone daily for one week in male veterans with chronic PTSD yields a sufficiently high proportion of clinical responders after one month to warrant more extensive and definitive research.

##### 1.c.2. *Secondary Objectives*

1.c.2.a. To study the trajectories of CAPS (past week symptom status) scores over the study duration for mifepristone (600 mg/day) and placebo.

1.c.2.c. To determine if a Phase III study is justified.

1.c.2.d. To compare study drug related adverse events (AEs) and serious adverse events (SAEs) in the two groups.

## 1.d. Outcome Measures

### 1.d.1. Primary Outcome

The primary clinical outcome measure will be the presence or absence of a clinical response, defined as a 30% or greater reduction in total CAPS (past week symptom status) score from baseline to four weeks.

### 1.d.2. Secondary Outcomes

The secondary outcome measures will be the changes in CAPS (past week symptom status) score from baseline to weeks 1, 4, and 12 to capture time by treatment interaction, the proportion of clinical responders at 12 weeks for deciding sustainability, and the percentage of study drug related AEs and SAEs to study safety and tolerability of mifepristone.

### 1.d.3. Descriptive Outcomes

The impact of mifepristone on other clinical parameters will be described, including the three PTSD symptom sub-scales from the CAPS (intrusion/re-experiencing, avoidance/emotional numbing, and hyperarousal), depression (Beck Depression Inventory (BDI)), PTSD (PTSD Checklist (PCL)), sleep quality (Pittsburgh Sleep Quality Index (PSQI)), anger (State-Trait Anger Expression Inventory (STAXI)) and functional impairment (functional impairment measure (item 24) on the CAPS). The neuroendocrine effect of mifepristone in PTSD will be assessed by measuring the changes in plasma cortisol and ACTH levels from baseline to immediately after one week of treatment and from baseline to four weeks. The relationship of plasma cortisol and ACTH levels to clinical response will also be explored. As an additional descriptive measure, plasma levels of mifepristone and its metabolites will be assessed immediately after one week of treatment, and its relationship to clinical response and the trajectories of CAPS scores will be assessed.

## 2. Background and Significance

### 2.a. Background

#### 2.a.1. Clinical and neuroendocrine profile of mifepristone

Animal and human studies have shown that mifepristone is a potent glucocorticoid receptor antagonist that blocks the effects of endogenous and exogenous glucocorticoids (i.e. cortisone, cortisol, and

[figure not shown]

dexamethasone) and has peripheral and central effects (Bertagna et al., 1984; Gaillard et al., 1984; Heikinheimo et al., 2003). Cortisol levels increase in response to acute HPA axis activation and then inhibit their further release through negative feedback inhibition of the HPA axis, as depicted in Figure 1. Accordingly, the acute blockade of GR by mifepristone and its metabolites which interrupts this negative feedback loop, results in a compensatory increase in cortisol and ACTH levels (Bertagna et al., 1984; Raux-Demay et al., 1990). While ambient cortisol levels increase with mifepristone, cellular assays reveal that mifepristone decreases peripheral glucocorticoid bioavailability through blockade of GR (Heikinheimo et al., 2003). At high doses

mifepristone crosses the blood-brain barrier, as evidenced by animal studies that demonstrate that there are comparable levels of drug in both plasma and brain (Sarker et al., 2002; Karssen et al., 2003). Mifepristone and its active metabolites inhibit the efflux of cortisol via the glycogen pump at the blood-brain barrier which facilitates the uptake of cortisol into the brain (Sarkar, 2002); brain levels are further increased due to the increased peripheral levels.

Mineralocorticoid receptors (MR), which are activated at lower doses of cortisol, help to maintain neuronal homeostasis and limit the disturbance caused by acute stress whereas GRs, which are occupied at higher levels of cortisol, help to facilitate recovery from a stressor. The balance of MR/GR-mediated actions is critical to homeostatic processes in the brain, and an imbalance leads to HPA axis dysregulation and associated aberrations in metabolism, immune function, and memory function (De Kloet and Derijk, 2004). The attendant shift in balance of MR/GR occupancy is hypothesized to recalibrate the HPA axis by normalizing

hormonal set points (Belanoff et al., 2002; Buckley et al., 2008) which could reverse some of the stress-related neurobiological and allostatic changes that are associated with this disorder. Since the HPA axis in PTSD appears to be dysregulated in a unique way, the full range of effects of GR antagonism in PTSD cannot be fully predicted based on animal studies or studies in major depression. A systematic, empiric approach is needed to examine the potential range of therapeutic effects in PTSD and their neuroendocrine correlates.

Mifepristone has been studied in psychotic major depression (PMD). PMD and PTSD are both characterized by elevated levels of CRH but many of the other neuroendocrine alterations are in opposite directions in these two disorders. Thus, efficacy or lack of it would not predict efficacy in the other disorder. The clinical trial data are summarized to highlight the existence of evidence for the central effects of mifepristone and recalibration of the HPA axis as well as abundant safety data (see section 2.a.3.).

The initial trials of mifepristone in PMD include: 1) a crossover trial in which mifepristone (600 mg/day x 4 days) was associated with rapid improvement in depression (Belanoff et al., 2001); 2) an open-label trial in which high dose mifepristone (600 mg/day or 1200 mg/day) for one week had substantial improvement in depression and psychosis compared to a low-dose mifepristone (50 mg/day) (Belanoff et al., 2002); and 3) a double-blind trial in which 7 of 15 in the mifepristone group showed a 50% reduction in psychotic symptoms compared to only 2 of 15 in the placebo group (Flores et al., 2006). The first Phase III trial was positive; in a double-blind trial of 221 patients with psychotic major depression, persons in the mifepristone group were significantly more likely to achieve a clinical response than those in the placebo group (DeBattista et al., 2006). In a subsequent Phase III trial of one week of mifepristone (600 mg/day), there was a site-by-treatment interaction (Blasey et al., 2009). In the initial 20 study sites involved from the trial outset, there was a significantly greater proportion of responders at day 56 in the mifepristone than the placebo group (26% vs. 13%). In contrast, in the 9 additional sites added to boost enrollment, there was a higher placebo response rate. An analysis of trough mifepristone levels, which was specified *a priori*, showed that the response rates were significantly higher in patients whose plasma mifepristone levels were at or above the pre-specified threshold level (1800 ng/ml) compared to placebo; the effect was evident both when examining the original sites in the study (active response vs. placebo response of 46% vs. 17%) and when all sites were included (41% vs. 23%) (Blasey et al., 2009).

The data demonstrate that mifepristone can induce beneficial clinical effects that persist beyond the period of active treatment (Belanoff et al., 2002; Young et al., 2004). It has been hypothesized that enduring effects of mifepristone may result from a recalibration of the HPA axis. One proposed mechanism is that the acute blockade of GR, increase in cortisol levels, and binding of cortisol to the MR (which are not blocked by mifepristone) would lead to the down-regulation of these receptors and a resetting of the HPA axis. Such effects are hypothesized to be enduring clinical effects that have been observed after drug discontinuation (Belanoff et al., 2002; Flores et al., 2006). Supporting this hypothesis, a recent analysis found that cortisol levels in patients with bipolar disorder and schizophrenia increased acutely following treatment with mifepristone (600mg/day x 7 days) compared to placebo; at day 21, cortisol levels had declined from baseline in the mifepristone group, suggesting normalization of the HPA axis (Gallagher et al., 2008). These data provide preliminary evidence that mifepristone can recalibrate the HPA axis and induce enduring therapeutic change in a way that may be relevant in the treatment of PTSD.

## 2.a.2. *Rationale for trial of mifepristone in veterans with PTSD*

### 2.a.2.a. Mifepristone and the neuroendocrinology of PTSD

Among the most replicated neuroendocrine findings in PTSD (the majority of which have been demonstrated in veterans) have been of elevated levels of corticotropin-releasing factor (CRF) in the cerebrospinal fluid (CSF) (Bremner et al., 1997; Baker et al., 2005) and an exaggerated suppression of cortisol to a low dose of the synthetic glucocorticoid dexamethasone (DEX). The finding of enhanced suppression of cortisol to low-dose DEX was first observed in Vietnam veterans with PTSD ([name] et al., 1993). With a few exceptions, greater suppression of cortisol to low-dose DEX has consistently been found in PTSD participants compared to unexposed and/or trauma-exposed controls without PTSD; the finding has also been demonstrated in samples of persons exposed to combat, natural disasters, domestic violence, the Holocaust, and childhood physical and sexual abuse (Newport et al., 2004; Griffin et al., 2005). More recent studies have demonstrated increased suppression of ACTH to DEX ([name] et al., 2004; Newport et al., 2004), confirming

increased glucocorticoid responsivity at the level of the pituitary. Enhanced negative feedback inhibition of the HPA axis in PTSD could help to explain why 24-hour basal cortisol levels are not typically elevated, and indeed are even sometimes low (reviewed in [name], 2002), despite evidence of central HPA axis activation and exaggerated HPA axis responsivity (Rasmusson et al., 2001; Bremner et al., 2003). It is presumed that the enhanced sensitivity to glucocorticoids reflects greater responsiveness of glucocorticoid receptors (GR), as suggested by changes in GR number and response following challenge with DEX ([name] et al., 2003). That enhanced GR responsiveness is a risk factor for PTSD has recently been confirmed in a large prospective study of deployment-related PTSD. Basal cortisol level was not a predictor of PTSD, but the number of lymphocyte glucocorticoid receptors was significantly higher in participants who developed PTSD symptoms following deployment than those who did not (van Zuiden et al., 2011). It has been hypothesized that enhanced GR responsiveness is a secondary adaptation to decreased hormone bioavailability (Raison and Miller, 2003), which is suggested by the finding of lower cortisol in some studies in PTSD ([name], 2002). Since mifepristone is a glucocorticoid receptor antagonist and increases brain cortisol it could be beneficial both with respect to enhanced GR sensitivity and inadequate signaling. Inadequate glucocorticoid signaling, whether as a result of low cortisol or other alterations, would set the stage for an inadequate response to acute stress and a failure to constrain stress responsive systems (reviewed in [name], 2009). Inadequate glucocorticoid signaling would in turn release the sympathetic nervous system (SNS) and CRH from inhibitory control, leading to increased sympathetic catecholamine levels (Raison and Miller, 2003), CRH levels (Bremner et al., 1997; Baker et al., 1999), and immune activation (Raison and Miller, 2003), which have been described in PTSD. Inadequate glucocorticoid signaling in the aftermath of trauma may result in a cascade in which there is increased SNS activation, leading to an exaggerated catecholamine response to the trauma, which in turn could initiate a process in which traumatic memories become “over-consolidated” or inappropriately remembered due to an exaggerated level of distress and arousal (Pitman, 1989). Failure to properly contain the SNS response to traumatic reminders could perpetuate the intrusive and hyperarousal symptoms of chronic PTSD, leading to the elaboration of avoidance symptoms that commonly occur in the disorder over years or even decades ([name], 2009).

#### 2.a.2.b. Potential mechanisms by which mifepristone could impact PTSD-associated alterations in brain function

Since GR and MR are expressed in key brain regions implicated in PTSD, normalization of HPA axis regulation could lead to symptomatic and cognitive improvement across multiple domains. Convergent structural and functional neuroimaging studies and neuropsychological studies support a model of altered neurocircuitry in PTSD best characterized by exaggerated amygdala responses and deficient prefrontal cortical (PFC) and hippocampal function (reviewed in Rauch et al., 2006). These brain regions express GR and MR and are regulated by glucocorticoids. It is not yet known to what extent impairments in the functioning of these brain regions or alterations in their circuitry are a function of aberrant neuroendocrine activity, nor to what extent these impairments contribute to the HPA axis alterations in PTSD. However, studies have demonstrated differential effects of exogenous glucocorticoids on declarative memory and working memory in PTSD, suggesting altered central sensitivity to glucocorticoids in PTSD, which may be mediated through effects on the hippocampus and amygdala (Bremner et al., 2004).

There is abundant evidence of impaired hippocampal function in PTSD, as suggested by impairments in explicit/declarative memory and paired associate learning (Gilbertson et al., 2001; [name] et al., 2003; Bremner et al., 2004). Imaging studies provide evidence of reduced hippocampal activation in response to cognitive activation techniques (Bremner et al., 2003), smaller hippocampal volumes (Gurvits et al., 1996; Stein et al., 1997), and decreased hippocampal N-acetyl aspartate (indicative of impaired neuronal integrity), which was positively associated with cortisol level in the absence of hypercortisolemia (Neylan et al., 2003). Although some of these hippocampal and HPA axis characteristics may reflect pre-morbid risk for PTSD (Gilbertson et al., 2002), they do not appear to be immutable. Indeed SSRI treatment of PTSD in civilians is accompanied by an increase in hippocampal volume, improved declarative memory performance, and reduced cortisol reactivity to stress (Vermetten et al., 2006). Thus, if there is altered glucocorticoid regulation of the hippocampus, GR blockade and the subsequent up-regulation of hippocampal MR could lead to improvement in PTSD-related symptoms and memory impairments. In animal studies, mifepristone reverses glucocorticoid-

mediated impairments in hippocampal morphology and function. For example, in rats, it protects against glucocorticoid-induced cell death in the hippocampus, fully reverses the deleterious effects of chronic stress on hippocampal synapses, and improves spatial memory, a hippocampal-dependent form of memory, when administered continuously (Oitzl et al., 1998).

Deficient activity of the medial PFC in response to aversive stimuli (Shin et al., 2005) has been observed in PTSD, and symptom improvement is associated with increased medial PFC activity (Seedat et al., 2004). PTSD is also associated with deficits in working memory (Vasterling et al., 1998; Stein et al., 2002), a memory process mediated in part by the PFC. In healthy adults, working memory is very sensitive to the effects of glucocorticoids (Lupien et al., 1999; Young et al., 1999), and working memory in PTSD participants is more sensitive to the effects of hydrocortisone than in healthy controls; this finding suggests the possibility of greater glucocorticoid sensitivity in this region. Altered activity of the amygdala in PTSD, evidenced by increased amygdala activity in response to traumatic reminders and aversive stimuli (Liberzon et al., 1999; Shin et al., 2005) has also been shown. Animal studies describe a complex interplay between the amygdala and the HPA axis, and their effects on memory. Glucocorticoids increase amygdala activation; amygdala activation can activate the HPA axis and the noradrenergic system which, through secretion of norepinephrine, can stimulate CRF release and further enhance cortisol secretion in a feed-forward system. In broad outline, such studies suggest that normalization of HPA axis activity would impact amygdalar activity, perhaps improving the associated anxiety and anger common in PTSD.

These human and animal studies demonstrate that there are multiple brain sites implicated in PTSD that have reciprocal interactions with the HPA axis, the normalization of which could impact PTSD-related symptoms, cognitive impairments, and HPA axis alterations. The full range of acute and chronic effects of GR antagonism in PTSD cannot be predicted based on either animal studies or studies in other human disease states since treatment with mifepristone would modulate glucocorticoid activity in multiple interconnected brain regions simultaneously in systems that are dysregulated, in a unique way, at baseline. Thus, a systematic, multidisciplinary approach is needed to examine the full range of clinical and neuropsychological effects of mifepristone in PTSD and their relationship to neuroendocrine effects.

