#### 4.f. Follow-Up Assessments

The study physician will assume the psychiatric care of the participant for the duration of the study. A research flag in the electronic medical record will be established for each patient to alert other providers to the veteran's participation in the study and of the need to refer psychiatric matters to the study physician. The patients other providers will also be informed of important clinical events by personal communication and/or through their inclusion as additional co-signers on research-related notes made in the electronic medical record.

As outlined in Table 2, the veteran will be assessed in person 48 to 72 hours after taking the first dose of the study drug. An ECG, vital signs (pulse, blood pressure, temperature), and medical labs (complete blood cell count, fasting glucose, cortisol, and electrolytes) will be taken. Any symptoms and changes in concomitant medications will also be reviewed. The checkup is intended for safety reasons. Follow ups will occur immediately after the pulsed treatment (one week follow-up), at one month follow-up, and at three month follow-up. At each of these three visits, the participant will be assessed for safety (adverse event reporting, vital

signs and weight, C-SSRS interview), PTSD and psychiatric status (CAPS and self-report measures), and concomitant medication use. In addition, blood will be drawn for medical labs (complete blood cell count, fasting glucose, and electrolytes) and neuroendocrine assessment (plasma cortisol and ACTH) at the day 3, one week and one month follow-up visits; an ECG will also be performed at the one week follow-up visit. Refer to figure 3 for a timeline of study visits.

In order to quantify the amount of co-therapy the participant receives during the study, the psychosocial treatment schedule provided in the Longitudinal Interval Follow-up Evaluation (LIFE) study will be used. With this instrument we will collect data about the types of therapy the veteran has received. Specifically, we will collect information about the number of sessions per week that the patient has had of the following types of therapy: individual, group, family, medication session, or self-help. The information will be collected at one month intervals (1 month follow-up (week 4, visit 4); 2 month follow-up telephone check-in (week 8, visit 6); 3 month follow-up (week 12, visit 8).

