#### 4.k. Outcome Assessment

The primary clinical outcome measure will be clinical response status at study endpoint (week 4), defined as a 30% or greater reduction in CAPS total score from baseline to week 4. Response status at week 12 will also be assessed as a secondary outcome measure. Total symptom severity during the prior week will be measured using the CAPS (Blake et al., 1995), a well-validated scale widely used in outcome studies of PTSD. PTSD symptom severity is calculated by summing the frequency and intensity rating of each of the 17 PTSD symptom items.

The secondary outcome measures will be the change in CAPS score from baseline to 1 week, 4 weeks and 12 weeks, the presence of clinical response as defined above at 12 weeks, and the percentage of study drug related AEs or SAEs.

The descriptive clinical outcome measures will be change from baseline to week 4 and week 12 for the following: the three PTSD symptom sub-scale scores from the CAPS, self-reported depression severity as measured by the BDI (Beck et al., 1996), PTSD symptom severity as measured by the PCL (Weathers et al., 1996), sleep quality as measured by the PSQI (Buysse et al., 1989), self-reported experience, expression, and control of anger as measured by the STAXI (Spielberger et al., 1988), and functional impairment as measured by item 24 of the CAPS.

Neuroendocrine outcomes include change from baseline to post-pulse treatment in plasma cortisol and ACTH levels. These will allow for assessment of the acute neuroendocrine response to 600 mg of mifepristone and its relationship to treatment outcome. Additionally, plasma levels of mifepristone and its metabolites will be assessed immediately after one week of treatment.

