- a. Descriptive statistics for the change in score from baseline to one month on the STAXI and confidence intervals will be provided for each treatment group.
- b. Change in score from baseline to one month on the STAXI will be compared between mifepristone and placebo using two-sample t-test (or Wilcoxon rank-sum test if the normality assumption does not hold).
6. Functional Impairment
- a. Descriptive statistics for the change in score from baseline to one month on the functional impairment measure (item 24) from the CAPS and confidence intervals will be provided for each treatment group.
- b. Change in score from baseline to one month on the functional impairment measure (item 24) from the CAPS will be compared between mifepristone and placebo using two-sample t-test (or Wilcoxon rank-sum test if the normality assumption does not hold).
7. Neuroendocrine
- a. Descriptive statistics for the change in score from baseline to one week following treatment, and baseline to one month and confidence intervals for plasma cortisol and ACTH levels will be provided for each treatment group.
- b. Change in plasma cortisol and ACTH levels from baseline to one week following treatment and baseline to one month will be compared between mifepristone and placebo using two-sample t-test (or Wilcoxon rank-sum test if the normality assumption does not hold).
- c. Mean plasma cortisol levels at one month will be compared between clinical responders (30% reduction in CAPS score) and non-responders using a t-test (or Wilcoxon rank-sum test if the normality assumption does not hold). This analysis will be limited to those on mifepristone only.
- d. Mean ACTH levels at one month will be compared between clinical responders (30% reduction in CAPS score) and non-responders using a t-test (or Wilcoxon rank-sum test if the normality assumption does not hold). This analysis will be limited to those on mifepristone only.
8. Mifepristone and its metabolites
- a. Descriptive statistics and confidence intervals for one week following treatment for plasma levels of mifepristone and its metabolites will be provided.
- b. Mean plasma levels of mifepristone and its metabolites at one week will also be compared between clinical responders (30% reduction in CAPS score) and non-responders using a t-test (or Wilcoxon rank-sum test if the normality assumption does not hold).

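### Items 7c and 7d relate one-month cortisol and ACTH to response in the mifepristone arm only, so any association found cannot be told apart from one that would exist without the drug

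*Protocol*

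**What the plan says.** The background in section 2.a.2.b says that a systematic approach is needed to "examine the full range of clinical and neuropsychological effects of mifepristone in PTSD and their relationship to neuroendocrine effects". Section 1.d.3 lists cortisol and ACTH among the descriptive outcomes and adds: "The relationship of plasma cortisol and ACTH levels to clinical response will also be explored". It names no arm. Section 4.k says of the hormone changes from baseline to the end of the pulse: "These will allow for assessment of the acute neuroendocrine response to 600 mg of mifepristone and its relationship to treatment outcome".

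Section 4.p.1, Descriptive Outcomes, item 7, turns this into analyses. Item 7c: "Mean plasma cortisol levels at one month will be compared between clinical responders (30% reduction in CAPS score) and non-responders using a t-test", with a rank-sum test as fallback. Item 7d does the same for the other hormone: "Mean ACTH levels at one month will be compared between clinical responders". Both items end with the same sentence: "This analysis will be limited to those on mifepristone only".

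Sampling is not restricted by arm. Section 4.f schedules "neuroendocrine assessment (plasma cortisol and ACTH) at the day 3, one week and one month follow-up visits" for participants generally, and Table 2 marks cortisol and ACTH at baseline, week 1 and week 4. (Table 2 has cortisol only at day 3, which does not matter here, because 7c and 7d use the one-month value.)

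**The concern.** A comparison of responders with non-responders inside one arm shows whether hormone level and response go together among people who took the drug. It does not show whether they go together because of the drug. One-month cortisol might be prognostic, or might move with symptom change whatever its cause. In either case the same difference would appear among placebo participants. The placebo arm is the only place in this trial to look, and a stated rule leaves it out.

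What is at stake is how much the exploration announced in sections 1.d.3 and 4.k can show. With the placebo comparison absent, a positive 7c or 7d gives the reader nothing to weigh against the explanation that the link is non-specific.

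**Working it through.** **Step 1. Does another planned analysis fill the gap?** The analyses in section 4.p.1 that come near it:

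| Item | Arms | Hormone | Linked to response or CAPS? |
|---|---|---|---|
| 7b | both | change in cortisol, ACTH | no, arms compared only |
| 7c, 7d | mifepristone | one-month cortisol, ACTH | yes |
| 8b | drug levels | none (mifepristone and metabolites) | yes |
| 8c | both | none (mifepristone and metabolites) | yes, CAPS trajectory |

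None estimates the cortisol or ACTH link with response on placebo, or its difference between arms.

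**Step 2. Inputs.** From section 4.n.2: 45 per arm, 20% attrition (45 × 0.8 = 36 completers per arm), 40% placebo response, and 40% + 15% = 55% on drug. From the end of section 4.p.1: two-sided 5% tests. The arm size reproduces: 72/(1 − 0.20) = 90. The exact probability of correct selection at 36 per arm, with ties split, is 0.899, in line with the stated 90%. The sample size is not in dispute.

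The documents give no figure for the size of the hormone link. I assume a responder minus non-responder gap d of 0.5, 0.8 or 1.0 SD.

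**Step 3. Same gap in both arms, so no drug-specific link** (8,000 simulated trials per setting; share significant at 5%):

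| Per arm | d | 7c/7d as planned | Arm-by-response contrast |
|---|---|---|---|
| 36 | 0.5 | 28% | 5.0% |
| 36 | 0.8 | 62% | 4.9% |
| 36 | 1.0 | 81% | 5.2% |
| 45 | 0.5 | 36% | 5.0% |
| 45 | 0.8 | 74% | 4.9% |
| 45 | 1.0 | 90% | 4.7% |

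The third column is the ordinary power of a test of association for a link that was put into the data. It is not a false-positive rate. The point is that the column would be the same if the link existed only on drug, because the mifepristone data are then identical in distribution. The planned test therefore cannot discriminate between the two cases.

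**Step 4. Precision of the contrast.** Expected cells at 36 per arm are 19.8 and 16.2 on drug, and 14.4 and 21.6 on placebo.

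- Drug difference: SE = √(1/19.8 + 1/16.2) = 0.335 SD; 95% half-width 1.96 × 0.335 = 0.66 SD.
- Placebo difference: SE = √(1/14.4 + 1/21.6) = 0.340 SD; half-width 0.67 SD.
- Contrast: SE = √(0.335² + 0.340²) = 0.477 SD; half-width 1.96 × 0.477 = 0.94 SD.

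At 45 per arm the contrast has half-width 0.84 SD.

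**Step 5. Power of the contrast when the link exists on drug only.** With assumed correlations between CAPS improvement and hormone level of 0.2, 0.3, 0.4 and 0.5 on drug and 0 on placebo, at 36 per arm (4,000 simulated trials each), the contrast is significant in 11%, 17%, 27% and 38% of trials.

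**The case against.** The protocol never says that 7c and 7d will establish a mechanism. Section 1.d.3 only promises to explore, section 4.k speaks of the response to mifepristone, and the end of section 4.p.1 calls the results hypothesis generating. Restricting to one arm also avoids mixing drug-altered and unaltered hormone axes. The contrast that would replace the restriction is weak, and responder status arises after randomisation in both arms, so the contrast is not a randomised comparison. All of this stands, and it keeps the point small. It does not justify leaving out the placebo result: reporting each arm separately mixes nothing and keeps the mifepristone finding.

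Stronger readings are tempting but not supported:

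- **That a positive 7c or 7d would drive the Phase III decision.** The signal rule in sections 4.n and 4.p.1 is the 15-point difference in responder rates; the hormone items play no stated part in it.
- **That the protocol itself shows cortisol moving with recovery.** Section 2.a.2.b reports "improved declarative memory performance, and reduced cortisol reactivity to stress" with SSRI treatment. That is reactivity to stress, not basal one-month level, and no correlation with response is given.
- **That the pilot shows no drug effect on week-4 cortisol.** The means were 11.53 on drug and 11.83 on placebo. The p-value of 0.786 tests the between-group difference in change from initial to 4 weeks with 4 per arm. It says little about a null, and nothing about association within an arm.
- **That the plan breaks a commitment in section 2.a.2.b.** That text is background and fixes no analysis.

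**Conclusion.** The point holds as a minor weakness in the choice of analysis. Items 7c and 7d, by a stated rule, omit the placebo comparison that a reader needs in order to interpret a hormone-response association, and nothing else in the plan supplies it. With an equal link in both arms, the planned test is significant in 28% to 90% of simulated trials, depending on an assumed gap of 0.5 to 1.0 SD and on 36 or 45 per arm. A significant result is therefore no evidence that the link is specific to the drug. The gap sizes and correlations are assumptions, since the documents give none; the arm sizes and response rates are the protocol's own.

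The primary decision rule and the safety analyses are unaffected. The remedy improves description, not proof: with a half-width of about 0.94 SD and 11% to 38% power under the drug-only settings examined, the contrast would miss such a link more often than not.

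**What to change.** In section 4.p.1, items 7c and 7d:

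1. Delete the sentence that limits the analysis to the mifepristone arm.
2. Report the responder minus non-responder difference in one-month cortisol and in ACTH, with its confidence interval, in each arm.
3. Add the arm-by-response contrast with its confidence interval, as a descriptive result.
4. State that an association within the mifepristone arm alone is not evidence of a drug-specific mechanism; that the contrast is imprecise, so a non-significant one does not rule such a link out; and that responder status is a post-randomisation variable.

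The cost is a few sentences and a few lines of code. No new samples are needed, since placebo cortisol and ACTH at one month are already required for item 7b.
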